##### Self-report

Self-reported primary outcome data will be verified in the medical records obtained from the hospital where the participant was recruited. Emergency department presentations will be captured for any health condition, or a complication of stroke, and are assumed to be unplanned. Hospital admission will be coded as unplanned if they are not clearly defined or flagged as planned, or meet any of the clinical conditions as recommended by the Australian Institute of Health and Welfare [12] and outlined below:At risk of serious morbidity/mortality and requiring urgent assessment and/or resuscitationHave suspected organ failure or system failureHave an illness or injury where the viability of a body part organ is acutely threatenedHave severe pain where the viability or function of an organ is suspected to be acutely threatenedHave significant haemorrhage and requiring urgent assessment and treatmentHave an acute condition which represents a significant threat to the patient’s physical or psychological wellbeingHave gynaecological or obstetric complications

After the trial is completed, an independent adjudication committee, who will remain unaware of the group allocation, will undertake a blinded adjudication of all hospital admissions within the 90-day post-randomisation period to ascertain whether admissions were planned or unplanned.

##### Administrative linked data

There will be linkage of trial participants with emergency department and hospital administrative data. Using these data, admission will be defined as “unplanned” if coded as “emergency admission — N1”, as recommended by the Australian Institute of Health and Welfare [12], or hospital admission within 24 h for any for the clinical conditions outlined above.

#### Secondary outcomes

The following secondary outcomes are being assessed at different points in the trial (Table 1):Weighted goal attainment scale (GAS) T-score is calculated based on data obtained across five domains (i.e. participant’s health, mind and body, everyday activities, out and about, and healthcare and support) using the GAS questionnaire [13].Change in the adoption of self-efficacy skills is being assessed using the Stroke Self-Efficacy Questionnaire. This 13-item questionnaire is used to collect information on the confidence of participants regarding undertaking tasks that may have been difficult due to the stroke [14].Change in mood, i.e. anxiety and depression, is being measured using the Hospital Anxiety and Depression Scale [15].Number of hospital contacts at 90 days post-randomisation: Composite outcome of number of self-reported emergency presentations or hospital admissions to be determined using self-reported or linked data.Change in health-related quality of life is being assessed using the EQ-5D-3L questionnaire [16], across five health domains (i.e. mobility, self-care, usual activities, pain/discomfort, and anxiety/depression), and overall using a visual analogue scale.Cost-effectiveness: Cost at 90-day and 12-month post-randomisation (self-reported resource use and/or administrative health service use data) per Quality Adjusted Life Year (QALY; derived from EQ-5D-3L questionnaire) gained.Patient education and self-management skills attainment at 90 days post-randomisation is being assessed with the Health Education Impact Questionnaire [17].Composite outcome at 90 days and 12 months post-randomisation: recurrent stroke, cardiovascular events or deaths. This will be determined using a combination of self-reported and linked data. Further details on analyses using linked data will be reported separately.Resource utilisation/costs will be measured using data on resource use that were self-reported and/or obtained from linked administrative records. Details on analyses of this outcome will be reported separately.Disability at 90-day post-randomisation assessed using the modified Rankin Scale [18].Unmet needs at 90-day post-randomisation: assessed using the Longer-term Unmet Needs after Stroke (LUNS) questionnaire [19].

### Analysis methods

All analyses will be based on the intention to treat principle, where participants will be analysed according to the group in which they were allocated, regardless of whether or not they received the intervention or deviated from the protocol. The proposed format for presenting study outcomes is shown in Tables 2 and 3.

**Table 2 Tab2:** Within- and between-group differences in primary outcome and categorical secondary outcomes

	Control (*N* =)			Intervention (*N* =)			OR (95% *CI*)^b^
	Baseline *n* (%)	90 days *n* (%)	Phi^a^	Baseline *n* (%)	90 days *n* (%)	Phi^a^	
Primary outcome							
Hospital presentation^c^	-		-	-		-	
Secondary outcomes							
Composite outcome^d^							
Problems in EQ-5D-3L dimension							
Mobility							
Self-care							
Usual activities							
Pain or discomfort							
Anxiety or depression							
Long-term unmet needs							

*OR* odds ratio, *CI* confidence interval, *EQ-5D-3L *EuroQol five dimensions three level. ^a^Measure of magnitude of within-group change at 90-day post-randomisation relative to the baseline measurement. ^b^Between-group difference at 90-day post-randomisation, adjusted for baseline measurements, clustering by recruitment hospital, and stratifying variables. ^c^Includes emergency department presentations and unplanned hospital admission. ^d^Comprises recurrent stroke, cardiovascular events, or deaths

**Table 3 Tab3:** Within- and between-group differences in non-categorical secondary outcomes

	Control (*N* =)			Intervention (*N* =)			Difference (95% *CI*)^c^
	Baseline Mean (SD)^a^	90 days Mean (SD)^a^	Cohen’s D^b^	Baseline Mean (SD)^a^	90 days Mean (SD)^a^	Cohen’s D^b^	
*Self-efficacy score*							
*Goal attainment scaling (T score)*							
Your health							
Mind and body							
Everyday activities							
Out and about							
Healthcare and support							
*Health education impact*							
Positive and active engagement in life							
Health-directed behaviour							
Skill and technique acquisition							
Constructive attitudes/approaches							
Self-monitoring and insight							
Health service navigation							
Social integration and support							
Emotional wellbeing							
*Mood*							
HADS depression							
HADS anxiety							
*EQ-5D-3L VAS*							
*Number of hospital presentations*							
Emergency department presentations							
Hospital admissions							
Modified Rankin Scale							

*SD* standard deviation, *CI* confidence interval, *HADS* Hospital Anxiety and Depression Scale, *EQ-5D-3L VAS* EuroQol five dimensions three level visual analogue scale. ^a^Data may also be presented as median and interquartile range, depending on the distribution of the outcome. ^b^Measure of magnitude of within-group difference at 90-day post-randomisation relative to the baseline measurement. ^c^Between-group difference at 90-day post-randomisation, adjusted for baseline measurements, clustering by recruitment hospital, and stratifying variables

#### Primary outcome

The primary outcome will be compared between groups using a mixed-effects logistic regression model, adjusted for clustering by recruitment hospital (random effect) and stratification variables, i.e. age and the level of disability (modified Rankin Scale) at baseline. The primary outcome model will be adjusted for stratification variables through either direct adjustment or inverse probability of treatment weighting, depending on the final sample or convergence of the models [20, 21]. If there are convergence issues, we will undertake an inverse probability of treatment weighting, involving the use of covariate values to predict the probability of participants being allocated to their respective group. This approach will be used to create a weighted trial sample, in which study groups have a similar distribution of the covariate values. The weights will then be applied to a simple mixed-effects logistic regression model.

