### Randomisation and blinding

Randomisation is undertaken through the REDCap online system [7], with stratification balancing by age (< 65 or 65+ years) and level of disability (based on a baseline modified Rankin Scale [scores 0–2 for none-minor disability, 3–4 for moderate-severe disability]). The randomisation table, comprising the allocation sequence, block sizes, and stratification balancing, was developed outside of REDCap by an independent data analyst and imported into the REDCap study database.

The trial has a double-blind design. Therefore, hospital staff, participants, outcome assessors, and trial biostatisticians are unaware of group allocation. To ensure that blinding of participants to group allocation is maintained, the trial is described in the patient information and consent form in general terms as “providing post-hospital discharge support” [8]. Specifically, intervention approaches were broadly described in the patient information and consent form as including the “setting of specific recovery goals with trained clinicians, receiving electronic self-management information sent via SMS or email, and participation in follow-up assessments”. Outcome assessors also use an interview script to standardise outcome assessments undertaken by telephone interview and are trained to avoid entering into general discussions. To ensure hospital clinicians and participants are unaware of the allocation group, all eligible consenting patients complete goal setting, using the ReCAPS “goal setting menu”, and data collection at baseline is standardised. The trial biostatistician who will undertake the analysis is also blinded to group allocation.

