### Sample size calculation

At the time we designed the trial, we were required to use indirect evidence to estimate the potential effect size of our novel intervention for the primary outcome. We estimated a sample size of 890 participants (445 participants in each intervention group) to allow sufficient power for the primary outcome analysis. The power calculation was based on the following: (a) a conservative estimate (33%) of participants in the control group having unplanned hospital presentations (emergency department/admission) within 90 days, based on data from the *Australian Stroke Clinical Registry* (*AuSCR*) linked to hospital emergency department presentations and admissions data in four states [1] and adjusted for the study inclusion criteria (being aged ≥ 18 years and discharged to home), (b) a 10% absolute reduction in unplanned hospital presentation (emergency department presentations or readmissions) within 90 days of randomisation in the intervention group vs. controls [9], (c) a ≥ 80% power at the significance threshold of *α* = 0.05 two-tailed and (d) an assumed attrition rate of 20% due to drop-out, refusal or loss to follow-up. Using an adaptive sample-size procedure we had pre-planned to re-estimate the sample size once, two-thirds of the original sample size outcomes had been obtained. Issues with recruitment during the COVID-19 pandemic and the current recruitment rate and available budget mean that this sample size is now infeasible to achieve.

The trial will be closed to recruitment by the end of December 2023, when our funding is expended with whatever number of participants is obtained by that time. This number will be used without any re-estimation of power. Using the observed data on retention rate (currently 93%), and more recent data on unplanned hospital presentations/readmissions from another study [10], our sample may provide sufficient power for a 10% difference in the primary outcome.

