### Timing of outcome assessments and final analysis

The primary outcome assessment is undertaken at 90 days (~13–15 weeks) after randomisation. The schedule of assessments for secondary outcomes ranges from baseline to 90 days post-randomisation and 12 months post-randomisation (Table 1). All outcome analyses will commence after all assessments and evaluations are completed.

**Table 1 Tab1:** List of study outcome

Assessment	Baseline	Follow-up^a^	
		90 days	12 months
Primary outcome			
Unplanned hospital presentation^b^		✓	
Secondary outcomes			
Goal attainment post-stroke^c^		✓	
Stroke self-efficacy^c^	✓	✓	
Anxiety and depression^c^	✓	✓	
Number of hospital contacts^d^		✓	✓
Health-related quality of life^c^	✓	✓	✓
Cost-effectiveness^c,d^	✓	✓	✓
Composite outcome^d,e^		✓	✓
Health education assessment post-stroke^c^	✓	✓	
Self-management post-stroke^c^	✓	✓	
Healthcare resource utilisation^c,d^	✓	✓	✓
Modified Rankin Scale^c^	✓	✓	
Long-term unmet needs^c^	✓	✓	

^a^Undertaken by blinded ReCAPS researchers at 90 days and 12 months post-randomisation. ^b^Includes emergency department presentations and unplanned hospital admission. ^c^Option for self-assessment by participants. ^d^Obtained through self-report and linkage with administrative data. ^e^Includes recurrent stroke, cardiovascular events, or deaths

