### Baseline patient characteristics

Data on baseline characteristics will be summarised as frequencies and proportions for categorical variables and medians and interquartile ranges for continuous variables (Supplemental Table II).

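### The primary model's only fixed covariates are the two stratification factors, apparently in binary form; using baseline values already collected would gain a little precision at almost no cost

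*SAP article*

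**What the plan says.** The Primary outcome paragraph under Analysis methods specifies a mixed-effects logistic regression "adjusted for clustering by recruitment hospital (random effect) and stratification variables, i.e. age and the level of disability (modified Rankin Scale) at baseline". If the model does not converge, inverse probability of treatment weighting replaces direct adjustment. No other prognostic covariate is named.

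Randomisation and blinding describes "stratification balancing by age (< 65 or 65+ years) and level of disability", with Rankin "scores 0–2 for none-minor disability, 3–4 for moderate-severe disability". Both factors are therefore binary at randomisation. The analysis section does not say whether they enter the model in that form.

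Table 1 ticks two relevant items at baseline: the modified Rankin Scale and "Healthcare resource utilisation". Exact age is not named as a collected variable. However, the age stratum cannot be assigned without knowing age, and the baseline section plans "medians and interquartile ranges for continuous variables".

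Footnote b of Table 2 says the odds ratios are also adjusted for baseline measurements. That column includes the primary outcome, whose baseline cells hold a dash. The table gives an odds ratio as the only between-group measure, while the hypothesis and the sample size are framed as a 10-point absolute reduction.

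**The concern.** Baseline predictors of the outcome that are already in the database can be put into the model at no cost to participants. They sharpen the treatment comparison and absorb chance imbalance. If age and Rankin enter as two-level factors, variation within each level goes unused, and prior healthcare use is not used at all. In a fully recruited trial this would hardly matter. This one closes at roughly half its planned size without re-estimating power, so small gains in precision are worth more than usual. Leaving the coding of the covariates unstated also leaves a choice open in the model that carries the trial's conclusion.

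**Working it through.** **Inputs from the SAP article.** Control risk: "a conservative estimate (33%) of participants in the control group having unplanned hospital presentations". Reduction: 10 points, so 33% versus 23%. Two-sided alpha 0.05, power at least 80%, attrition 20%, planned N 890 (Sample size calculation). Observed retention 93% (same section). Randomised 462 (Current status of the trial).

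**1. The planned size.** With mean risk 0.28, n per arm = [1.96·√(2·0.28·0.72) + 0.8416·√(0.33·0.67 + 0.23·0.77)]² / 0.10² = (1.2445 + 0.5311)² / 0.01 = 315.3, so 316. Then 632/0.8 = 790 (838 with continuity correction). The plan's 890 is larger: 890 × 0.8 = 712, or 356 per arm, which gives 84.6% power. That meets the stated condition of at least 80%, so 890 is conservative and not an error.

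**2. The achieved size.** 462/890 = 51.9%. 462 × 0.93 = 429.7, so about 430 analysable, 215 per arm. Power = Φ[(0.10·√215 − 1.2445)/0.6310] = Φ(0.351) = 63.7%. For the same 10-point difference it is 73.8% if the control risk is 25% and 58.5% if it is 40%. Expected events: 430 × 0.28 ≈ 120, ample for treatment plus three covariates.

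**3. What fuller adjustment adds.** The document gives no covariate strengths, so they are assumed and varied. Both simulations use 430 participants and marginal risks of 33% and 23%.

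*Simulation A*: 6,000 trials per row, stratified 1:1 allocation, no hospital effect. Age has mean 68 and SD 13, Rankin is 0–4, and prior use is a yes/no variable with 35% prevalence. All of these are assumptions. Entries are power (%).

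| AUC of covariates | Binary strata | Full age and Rankin | Plus prior use | Total gain (points) |
|---|---|---|---|---|
| 0.50 | 64.6 | 64.5 | 64.5 | −0.1 |
| 0.56 | 63.8 | 63.6 | 63.7 | −0.1 |
| 0.62 | 64.5 | 64.6 | 65.2 | 0.7 |
| 0.68 | 63.8 | 64.6 | 65.8 | 2.0 |
| 0.75 | 66.2 | 66.8 | 71.0 | 4.8 |

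The Monte Carlo standard error of one entry is √(0.64·0.36/6000) ≈ 0.6 points.

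*Simulation B*: 4,000 trials per setting, three independent standard-normal predictors, binary two-factor model against the full continuous model with prior use. Power moves from 64.1 to 65.0 (c-statistic 0.65), 65.7 to 68.2 (0.69) and 65.6 to 71.4 (0.74). The gains are 0.9, 2.5 and 5.8 points.

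**4. Where the gain comes from.** In simulation A, undoing the dichotomy adds at most 66.8 − 66.2 = 0.6 or 64.6 − 63.8 = 0.8 points. In the strongest row, prior use adds 71.0 − 66.8 = 4.2 points.

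**5. The odds ratio.** In simulation A the same marginal risks correspond to a conditional log odds ratio of −0.500 with no prognostic covariates and −0.593 in the strongest row, that is, odds ratios of 0.61 and 0.55. The conditional odds ratio therefore depends on what is adjusted for, while the marginal risk difference stays at 10 points.

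**The case against.** The strongest reply is that this is a preference about efficiency. A model with a hospital random effect and both stratification factors is valid, common and pre-specified. Binary coding is inferred, not stated. The benefit is small in most settings. Both simulations also favour the richer model, because covariate effects are exactly linear on the log-odds scale and the predictors are independent. Entering Rankin as a linear score is itself an assumption. All of this stands and limits the size of the point.

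Two stronger readings are tempting. First, a reader might infer that the plan omits the baseline value of its primary outcome while adjusting secondary outcomes for theirs. The document does not support this. Table 1 has no baseline tick for unplanned presentation or for number of hospital contacts, Table 2 has dashes there, and the secondary-outcome rule concerns change from a baseline measure. Healthcare resource use is only a related predictor. Its content and look-back period are not given, and it comes partly from linked data whose analysis is reported separately.

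Second, a reader might infer from the textbook figure for a median split of a normal variable (2/π, about 64% of the information kept) that over a third of the covariate information is lost. Nothing shows that the cuts fall at medians, and Rankin 0–4 is a five-level scale. The loss in power for the treatment effect is at most about 1 point.

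The reply does not remove the practical case: with weak or null covariates the richer model shows no material loss, and the change needs no new data.

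**Conclusion.** The point holds as a modest efficiency improvement plus an unstated coding, not as an error or a source of bias. The word only applies to fixed covariates, since the hospital effect is in the model. The expected gain is about 0 to 2 points of power with weak to moderate predictors (2.5 points in one setting at a c-statistic of 0.69) and about 5 to 6 points if they are strongly prognostic. Most of it comes from prior healthcare use. These figures rest on assumed covariate strengths and on the design risks of 33% and 23%.

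A reader might infer that better adjustment could make up for the recruitment shortfall. It cannot: no simulated setting reaches 80%, and the fall from 84.6% to about 64% is due to sample size.

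**What to change.** Before unblinding, amend the Primary outcome paragraph under Analysis methods as follows:

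- Enter age as continuous and baseline modified Rankin as its full score, and state the coding of both.
- Add self-reported baseline hospital or emergency department use as a named fixed covariate, provided the baseline resource-use form captures it for all participants. If it does not, leave it out.
- Keep the strata-only model as a sensitivity analysis.
- Report a standardised (marginal) risk difference with 95% confidence interval beside the odds ratio, so that the result can be read on the 10-point design scale.
- Make footnote b of Table 2 agree with the final covariate list for the primary outcome.

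The cost is some SAP wording and a few model terms. The article describes the analysing biostatistician as blinded and expects data lock in the second quarter of 2024, which leaves room for the change. The small downside is that the conditional odds ratio changes meaning slightly; the marginal risk difference addresses this.

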#### Secondary outcomes

Generalised mixed-effects regression models (including linear, logistic, quantile or negative binomial regression) will be used to compare secondary outcomes between allocation groups, depending on the nature and distribution of these outcomes. Models will be constructed using similar procedures specified for the primary outcome analysis. For comparison of changes in a secondary outcome measure from baseline between groups, regression models will comprise the outcome measure at the time of follow-up as the dependent variable, the group allocation as the independent variable, and the baseline measure of the outcome as a covariate. The magnitude of change from baseline within groups will be estimated as Cohen’s d for continuous or ordinal variables, or Phi co-efficient for categorical variables, based on outputs from the regression models.

### Sensitivity/subgroup analyses

We will undertake per-protocol analyses (described above) for all outcomes. Further, a limited number of unadjusted subgroup analyses will be undertaken regardless of the effect of the intervention on the primary outcome. These include analyses stratified by age (< 65 years *vs*. ≥ 65 years), sex (male *vs*. female), level of disability (modified Rankin Scale score ≤ 2 *vs*. > 2), living condition (living alone *vs*. with carer/family), educational attainment (university education *vs*. no university education), preferred mode of communication (SMS *vs*. email), and number of goals set (≤ 3 *vs*. > 3 goals). Apart from these pre-specified subgroup analyses, exploratory analyses may also be undertaken, informed by variables with significant statistical interaction with the intervention.

### Missing data

The primary analysis will be reported without imputation of missing data. However, if the proportion of missing primary outcome measure exceeds 10%, we will undertake multiple imputation of these missing data. This will involve multivariate imputation by chained equations algorithms, where the imputed value is conditional on observed values of other baseline variables [22]. This algorithm will be repeated for up to 20 cycles to obtained imputed values for the first imputed dataset. To ensure robustness of this imputation process, this process will be repeated to obtain 20 imputed datasets. The pooled estimate from these imputed datasets will be reported and compared with unimputed primary outcome model. We will also explore other imputation approaches for the primary outcome, including imputing missing values as either 0 or 1. Missing secondary outcomes will be imputed using multivariate imputation by chained equations algorithms.

